## Abstract

**Background:**

Warfarin is an oral anticoagulant medication that disrupts the liver’s production of clotting factors. While this medication is highly effective for the prevention of thromboembolic events, it also has a narrow therapeutic range and a vulnerability to interactions with other drugs and vitamin K-containing foods. Warfarin is commonly ingested at dinnertime, the same time of day that dietary vitamin K consumption (found largely in green leafy vegetables) is most variable. While the long half-life of warfarin might make this irrelevant, the ultra short half-life of vitamin K and the possibility of a hepatic first-pass effect for warfarin make it worth evaluating whether morning ingestion of warfarin, when vitamin K levels are consistently low, leads to greater stability of its anticoagulant effect. An examination of the timing of administration on the effectiveness of warfarin has never before been conducted.

**Methods/design:**

This is a 7-month Prospective Randomized Open Blinded End-point (PROBE) study in which established evening warfarin users (primary care managed Canadian outpatients in the provinces of British Columbia and Alberta) will be randomized to either switch to morning ingestion of warfarin (the intervention) or to continue with evening use (the control). The primary outcome is the percent change in the proportion of time spent outside the therapeutic range of the international normalized ratio (INR) blood test. Secondary outcomes include change in proportion of time spent within the therapeutic INR range (TTR), percentage of patients with TTR >75 %, percentage of patients with TTR <60 %, and major warfarin-related cardiovascular events (including all-cause mortality, hospitalization for stroke, hospitalization for GI bleeding, and deep venous thrombosis/pulmonary embolism). We will also compare whether day-to-day variability in the consumption of high vitamin K-containing foods at baseline affects the baseline TTR in this cohort of evening warfarin users.

**Discussion:**

This study addresses whether the timing of warfarin ingestion influences the stability of its anticoagulant effect. Should morning ingestion prove superior, the safety and effectiveness of this medication, and hence the prevention of stroke, pulmonary embolus, and major hemorrhage, could potentially be improved with no added cost or inconvenience to the patient.

**Trial registration:**

ClinicalTrials.gov: NCT02376803. Registered on 25 February 2015.

**Electronic supplementary material:**

The online version of this article (doi:10.1186/s13063-016-1516-9) contains supplementary material, which is available to authorized users.

## Background

Vitamin K is obtained primarily from green leafy vegetables (in particular kale, spinach, chard, beet greens, broccoli, cabbage, romaine lettuce, and Brussels sprouts) [1]. It is an essential cofactor used by the liver to “activate” the clotting factors it releases into the blood. Vitamin K has a very short half-life in the body (approximately 2 ½ hours) and cycles through an active (so far as its ability to “activate” clotting factors) and inactive form in the liver [2]. Warfarin acts by preventing one of the intermediary steps necessary to convert the inactive form of vitamin K back to the active form and hence it reduces the amount of available activated clotting factor [1]. When vitamin K is first ingested, however, it is in an easily activated form upon which warfarin has little effect [2]. As a result, consumption of high vitamin K-containing foods can counteract the effect of warfarin, and highly variable consumption of these foods may cause clinically important INR variability in some individuals [3].

The effectiveness of the anticoagulant warfarin is measured by the international normalized ratio (INR) blood test, which indicates how long it takes the user’s blood to clot compared to normal [1]. Canadian warfarin users typically have their INR measured by their family physician every 1–4 weeks, and same-day changes in warfarin dosing are made in response to that day’s INR test. In order to shorten the response time for making a dosing change, patients are traditionally advised to have their INR test in the morning and to take their warfarin in the evening (so that the INR test result will be back in time to change that day’s warfarin dose if needed). However, this leads to taking warfarin at the same time of day as the most highly variable consumption of vitamin K. Conceivably, if warfarin activity is greater around the time of ingestion, when liver concentrations would be highest, taking warfarin in the morning (when the vitamin K content of typical breakfast foods is consistently low) might lead to greater stability in anticoagulant effect. The question of whether the time of ingestion of warfarin matters to INR stability has never been formally addressed.

We are conducting a pragmatic randomized controlled trial (RCT) of morning versus evening warfarin ingestion to determine whether the timing of warfarin ingestion matters to the stability of its anticoagulant effect.

### Hypotheses

Our hypotheses are as follows:Morning, as compared to evening, administration of warfarin will produce a more consistent anticoagulant effect and improve the proportion of time a patient spends in the target therapeutic INR range (TTR = time in therapeutic range).A less variable day-to-day dietary vitamin K consumption at dinner, whether consistently high or consistently low, will reduce variability in the anticoagulant effect of warfarin and improve the proportion of time a patient spends in the target therapeutic INR range.

### Aims

This study has the following aims:To determine (by RCT) whether switching current warfarin users from evening to morning dosing will alter the proportion of time spent in the therapeutic INR rangeTo determine (by cross-sectional analysis of baseline data) whether evening warfarin users with greater variability in daily dinnertime vitamin K ingestion have a lower time in the therapeutic INR rangeTo determine by prospective subgroup analysis of RCT data whether the effect of warfarin timing on TTR (i.e., the effect of changing to morning dosing) is influenced by day-to-day variability in vitamin K consumption.

## Methods/design

### Study design

This is a Prospective Randomized Open Blinded End-point (PROBE) study [4] conforming to Consolidated Standards of Reporting Trials (CONSORT) guidelines. A CONSORT Flow Diagram is included as Additional file 1.

Ethics approval was obtained from the Health Research Ethics Board at the University of Alberta (Pro00050057) and the Clinical Research Ethics Board at the University of British Columbia (H14-03124). No modifications to the approved protocol are anticipated.

### Recruitment

Participating community family physicians in the Canadian provinces of British Columbia and Alberta will send a letter of invitation to all warfarin-using patients under their care with the exception of those whom they view as palliative or deemed incapable of informed consent. This letter: (1) describes the project, (2) lets patients know their physician’s office is participating, and (3) provides a central contact number that reaches our study coordinator for more information if they are interested. The study coordinator dialogs with interested patients who call in, screens them for eligibility, and obtains written informed consent (via online REDCap survey or mail-in consent form) from all patients willing to be randomized. For consenting participants who meet the screening criteria for eligibility, the family physician will be asked to provide investigators with the participant’s target INR range and their last 6 months of INR results, test dates, and warfarin dosing.

### Data collection and management

Study data will be collected, managed, and securely maintained using REDCap electronic data capture tools hosted by the Women and Children's Health Research Institute at the University of Alberta [5]. Non-electronic personal information of potential and enrolled patients (consisting of INR results and INR flow sheets faxed to us by family physicians) will be kept in a locked fireproof cabinet accessible only to the study investigators and staff. All study data (including INR results) will be archived in REDCap and maintained for a minimum of 5 years.

### Inclusion and exclusion criteria

Study inclusion criteria include: (1) dinner or evening use of warfarin, (2) ≥3 months of continuous warfarin use, (3) expectation of long-term warfarin use, (4) baseline INR data (last 6 months if available, minimum 3 months) with at least four evaluable INR results no more than 8 weeks apart provided to the study team by patient’s family physician, and (5) community dwelling. Exclusion criteria include patients under palliative care or those who are unable to provide informed consent in the opinion of the treating family physician.

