### Randomization and allocation

Upon receiving eligible baseline INR data, consented eligible participants are contacted by a study coordinator via telephone to obtain baseline information presumed to be predictive of TTR. This includes age ≥80 years, hospitalization in the last 6 months, temporary planned discontinuation of warfarin in the last 6 months (e.g., for elective surgery), number of daily prescription medications, <6 months of warfarin use, the self-reported average number of days per week in which high vitamin K-containing foods are consumed, and how variable the participant feels this estimated level of vitamin K consumption is (on a 4-point scale). This study coordinator (who has no clinical patient interactions) then randomizes the participant, using the REDCap^TM^ randomization module to ensure allocation concealment, to intervention or control [5]. Randomization will employ variable blocks of 2 or 4 and will be stratified by the proportion of baseline INR readings within the therapeutic range (<50 %, 50–80 %, >80 %).

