### Intervention and blinding

Active arm subjects will switch their warfarin use to morning. The control arm will continue with their current pattern of evening use. There are no run-in or washout periods in this study. Participants randomized to morning warfarin ingestion will be asked to make the change 5 days prior to their next scheduled INR test (so that any deviation in the INR can be detected early). Although patients and their physicians will be aware of treatment assignment, our study evaluators will be blinded to allocation.

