### Outcomes

Seven months after randomization of each patient, we will ask their family physician to provide us all INR results for that period in order to determine the following outcomes during the last 6 months of therapy.

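### For patients with 3 to 6 months of warfarin use the baseline INR window can include initiation, which costs the primary analysis some precision but does not bias it

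*Protocol article*

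**What the plan says.** All places are in the protocol article.

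- **Inclusion and exclusion criteria.** Criterion 2 asks for "≥3 months of continuous warfarin use". Criterion 4 asks for "baseline INR data (last 6 months if available, minimum 3 months) with at least four evaluable INR results no more than 8 weeks apart". Neither sets aside the first weeks on the drug.
- **Abstract, Methods/design.** The population is described as "established evening warfarin users".
- **Recruitment.** The family physician supplies 6 months of INR results, test dates and dosing. A warfarin start date is not listed.
- **Randomization and allocation.** "<6 months of warfarin use" is recorded at baseline as one of the factors presumed to predict TTR. Randomization is "stratified by the proportion of baseline INR readings within the therapeutic range", not by duration of use.
- **Intervention and blinding.** "There are no run-in or washout periods in this study".
- **Outcomes.** Seven months after randomization the INR results are collected "in order to determine the following outcomes during the last 6 months of therapy".
- **Primary outcome; Statistical analysis, RCT.** The endpoint is the percentage change in time out of range, compared by t test or Mann-Whitney U test. No covariate is named.
- **Baseline cross-sectional analysis.** Under 6 months of use is a covariate in the regression of baseline TTR.

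**The concern.** For a patient about 3 months into therapy, the shortest permitted baseline is the whole of the exposure. For one between 3 and 6 months, the request for 6 months of results also reaches the first dose, provided the records go back that far. In those weeks the INR is rising from untreated values and the dose is still being found, so the patient is likely to be out of range more than later.

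The two windows are not alike. Follow-up leaves out the first month after randomization and contains no initiation; baseline has no such protection. Because the endpoint is a percentage change, an inflated baseline does two things in these patients. Their out-of-range time falls in either arm without any effect of timing, which spreads the outcome. And a true proportional benefit on stable control is divided by too large a denominator, so it shows up smaller. The plan itself presumes that short use predicts TTR, yet does not use this in the randomized comparison.

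**Working it through.** **1. The plan's own figure.** Inputs from Sample size: difference 20, SD 40, power 0.90, alpha 0.05 (taken as two-sided). By the normal approximation, n per group = 2 × (1.960 + 1.282)² × 40² / 20² = 84.1, rounded up to 85. This reproduces the stated 85 per group and 170 in total. Power at 85 per group is 0.903. Going from 170 to 200 implies a 15 % dropout allowance (170 / 0.85 = 200).

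**2. Spontaneous fall in one recent starter.** The protocol gives none of these inputs, so all are assumptions: L = baseline length in weeks; w = weeks of initiation inside it (2 to 6); I = fraction out of range during initiation (60 to 80 %); S = fraction out of range afterwards (25 to 45 %).

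Baseline B = [w × I + (L − w) × S] / L, and fall = 1 − S / B.

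| L | S | I | w | B | Fall |
|---|---|---|---|---|---|
| 13 | 0.45 | 0.60 | 2 | 0.473 | 4.9 % |
| 13 | 0.35 | 0.60 | 4 | 0.427 | 18.0 % |
| 13 | 0.35 | 0.80 | 4 | 0.488 | 28.3 % |
| 13 | 0.25 | 0.80 | 6 | 0.504 | 50.4 % |
| 26 | 0.45 | 0.60 | 2 | 0.462 | 2.5 % |
| 26 | 0.35 | 0.60 | 4 | 0.388 | 9.9 % |
| 26 | 0.35 | 0.80 | 4 | 0.419 | 16.5 % |
| 26 | 0.25 | 0.80 | 6 | 0.377 | 33.7 % |

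The range is about 5 to 50 % at 13 weeks and 2.5 to 34 % at 26 weeks.

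**3. Dilution.** Suppose morning dosing cuts stable out-of-range time by a proportion r. A starter's change is S/B − 1 in the control arm and S(1 − r)/B − 1 in the morning arm. The difference is r × S/B. With r = 20 % and a fall of 20 %, S/B = 0.80 and the visible effect is 16 points; with a fall of 30 % it is 14 points.

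**4. Trial level.** Let f be the share of recent starters (assumed) and d their fall in points. Both arms shift by f × d on average. The SD becomes √[40² + f(1 − f)d²], taking 40 as the SD without starters. The diluted effect is 20 × (1 − f × d/100).

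| f, d | Mean fall, both arms | SD | n per group for a 20-point effect | Power at 85, SD only | Diluted effect | Power at 85, SD and dilution |
|---|---|---|---|---|---|---|
| 10 %, 20 | 2 | √1636 = 40.4 | 86 | 0.897 | 19.6 | 0.885 |
| 20 %, 20 | 4 | √1664 = 40.8 | 88 | 0.892 | 19.2 | 0.866 |
| 30 %, 30 | 9 | √1789 = 42.3 | 94 | 0.869 | 18.2 | 0.801 |

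If all 200 enrolled were analysed (100 per group), power with SD and dilution would be 0.929 in the first case and 0.861 in the last.

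**5. Bias.** In 20,000 simulated trials with no treatment effect and 85 per group, the mean between-arm difference was about 0. Type I error was 0.051 (f = 10 %, d = 20) and 0.048 (f = 30 %, d = 30).

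**The case against.** The strongest case for leaving the plan as it is has five parts.

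- **Randomization protects the comparison.** The fall is expected equally in both arms, so the contrast is unbiased. This stands. A reader might set the 18 to 28 % fall of the central 13-week case beside the 20 % target and infer that initiation alone could produce the effect sought. It could not: the target is a between-arm difference, whereas the fall is a within-patient change common to both arms. Nor can the protocol yield any single figure for the fall.
- **Few patients may be affected.** All warfarin users in a practice are invited and long-term use is expected. Nothing suggests a 30 % share of recent starters, and the share is not given. Where initiation was managed elsewhere, the family physician's records may begin later. This stands and limits the size.
- **The baseline regression is already protected.** A reader might infer that initiation confounds the dietary analysis of Aim 2. The under-6-months covariate largely deals with that, although one binary term treats a 3-month and a nearly 6-month user alike.
- **Stratification helps.** Starters with poor baseline control tend to fall in the low stratum, which partly balances them between arms. It removes neither the added spread in the unadjusted test nor the dilution.
- **Broad entry suits a pragmatic trial, and a sensitivity analysis could sit in an analysis plan that is not shown.** That is fair as to who is enrolled. It does not answer the baseline rule itself, which the article fixes and which decides what the primary outcome is divided by.

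**Conclusion.** The point holds as a modest weakness in how the baseline is fixed, not as a threat to validity. For patients with 3 to 6 months of use whose records reach back to the start, the denominator of the primary outcome is not stable evening dosing. The plan presumes that short use matters but does not use it in the randomized comparison.

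The loss is small if about 10 % are recent starters (power 0.885 to 0.897 against 0.903 at 85 per group, for a 20-point fall). It is material only if they are common (about 0.80 at 30 % starters with a 30-point fall and dilution). These figures rest on assumed initiation length, out-of-range fractions and share of starters, and on an SD of 40 that the plan itself adopts without prior data. They also keep the within-patient SD the same in starters as in others. Within-arm changes from baseline would be inflated in both arms and should not be read as effects.

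**What to change.** - **Baseline rule.** For patients with under 6 months of use, begin the baseline INR window a fixed, pre-specified period after the first warfarin dose. Require the 3 months of data and the four evaluable INRs to fall after that date, and align criterion 2 with this.
- **Patients already enrolled.** Recompute their baseline from post-initiation readings, using the INR dates and dosing that the family physician supplies.
- **Analysis.** Adjust the primary analysis for the recorded flag for under 6 months of use, or pre-specify a sensitivity analysis that leaves those patients out.

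The cost is low, and no treatment changes. The start date must be obtained or inferred, because the article does not list it among the data collected. Some recent starters would enter a few weeks later, and some already enrolled would have a shorter usable baseline. Recruitment began in February 2015, so a changed entry criterion would apply to only part of the cohort; the recomputed baseline and the analysis step keep the handling consistent across all patients.

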### Randomization and allocation

Upon receiving eligible baseline INR data, consented eligible participants are contacted by a study coordinator via telephone to obtain baseline information presumed to be predictive of TTR. This includes age ≥80 years, hospitalization in the last 6 months, temporary planned discontinuation of warfarin in the last 6 months (e.g., for elective surgery), number of daily prescription medications, <6 months of warfarin use, the self-reported average number of days per week in which high vitamin K-containing foods are consumed, and how variable the participant feels this estimated level of vitamin K consumption is (on a 4-point scale). This study coordinator (who has no clinical patient interactions) then randomizes the participant, using the REDCap^TM^ randomization module to ensure allocation concealment, to intervention or control [5]. Randomization will employ variable blocks of 2 or 4 and will be stratified by the proportion of baseline INR readings within the therapeutic range (<50 %, 50–80 %, >80 %).

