### Trial status

Recruitment started in February 2015. Patients are still being recruited at the time of submission.

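### Blocks of 2 or 4, with the coordinator who interviews the patient also randomizing in an open trial, leave many assignments predictable; the REDCap module alone does not ensure concealment

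*Protocol article*

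**What the plan says.** All references are to the protocol article.

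- **Block sizes** (Randomization and allocation): "Randomization will employ variable blocks of 2 or 4". The three strata are defined by the share of baseline INR readings in range: below 50 %, 50 to 80 %, and above 80 %. No other stratification factor is listed.
- **Who allocates** (same section): after eligible baseline INR data arrive, "consented eligible participants are contacted by a study coordinator via telephone to obtain baseline information presumed to be predictive of TTR". Next, "This study coordinator (who has no clinical patient interactions) then randomizes the participant", "using the REDCap^TM^ randomization module to ensure allocation concealment".
- **Who screens** (Recruitment): "The study coordinator dialogs with interested patients who call in, screens them for eligibility, and obtains written informed consent". The family physician is asked for the INR history only once the patient has consented and passed screening.
- **Blinding** (Intervention and blinding): patients and physicians know the assignment; the study evaluators do not.
- **Timing** (Trial status): "Patients are still being recruited at the time of submission".

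**The concern.** Concealment has two parts: the list must be hidden, and the next entry must not be inferable from entries already seen. A central module secures the first. The second depends on the block sizes and on what the person allocating has seen.

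Here the person allocating sees each result as it is issued. The baseline INR data are in hand before the call, so the next patient's stratum can be worked out in advance. With blocks of at most 4, an imbalance of two within a stratum fixes the next assignment, and an imbalance of one makes it likely.

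At stake is whether anything done just before allocation could depend on the coming arm: which eligible patient is called next and when, how a wavering patient is handled, and how the self-reported diet items are recorded. Those items are the number of days per week with high vitamin K foods and the 4-point variability rating. Both feed the planned subgroup analysis of the timing effect.

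**Working it through.** **The plan's own figures.** The article gives none for predictability. Its sample size reproduces (difference 20, SD 40, two-sided alpha 0.05, power 0.9: 85 per group, 170 in total) and is not affected. Only the enrolment target of 200 is used below, to turn shares into counts.

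**Inputs.** Blocks of 2 or 4, three strata, 1:1 allocation (article). Equal probability of each size (assumed; not stated). An observer who knows the possible sizes and all past assignments in the stratum, but not which size is running (inferred).

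**Rule.** Guess the arm that is behind in the stratum; guess at random when the arms are level. Each block ends level, so the imbalance in the stratum equals the imbalance in the current block.

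**Correct guesses per block.**
- Block of 2: 0.5 + 1 = 1.5.
- Block of 4: first 1/2; second 2/3; third 1/3 × 1 + 2/3 × 1/2 = 2/3; fourth 1. Sum 2.833.
- Equal mixing: (1.5 + 2.833) / 6 = 72.2 %.

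**Certain assignments.** An imbalance of two can occur only in a block of 4, with probability 1/3. It fixes the third and fourth assignments: 2 × 1/3 = 0.667 per block of 4, and 0.667 / 6 = 11.1 %.

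**Highly predictable assignments.** After the first assignment of a fresh block, the other arm follows with probability 1/2 × 1 + 1/2 × 2/3 = 0.83. With equal mixing, every assignment made while the arms are uneven therefore reaches at least 0.8. Their number per pair of blocks is 1 (block of 2) plus 1 + 1/3 + 1 (block of 4) = 3.33, and 3.33 / 6 = 55.6 %. Guesses among them are right 3 / 3.33 = 90 % of the time.

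**Simulation check.** 200 patients, three strata, 800 repetitions, best possible guess:

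| Blocks | Correct | Certain | Predictable at ≥ 0.8 |
|---|---|---|---|
| 2 only | 75 % | 50 % | 50 % |
| 4 only | 71 % | 33 % | 33 % |
| 2, 4 | 72 % | 10.8 % | 55 % |
| 4, 6 | 69 % | 5.6 % | 27 % |
| 4, 6, 8 | 68 % | 2.4 % | 24 % |
| 6, 8, 10 | 66 % | 1.7 % | 15 % |

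Uneven strata (20/50/30 %) give the same picture: 72.0 % correct and 10.9 % certain for blocks of 2 and 4.

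**As counts of 200.** Certain: 0.108 × 200 ≈ 22 now, against 0.024 × 200 ≈ 5 with blocks of 4, 6 and 8. Highly predictable: 0.55 × 200 = 110, against 0.24 × 200 = 48.

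**Sensitivity to the mixing probability.** Let p be the probability that a block has size 4. Correct = (1.5(1 − p) + 2.833p) / (2 + 2p); certain = 0.667p / (2 + 2p).
- p = 0.25: 73.3 % and 6.7 %.
- p = 0.75: 71.4 % and 14.3 %.

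**The case against.** The strongest reply is that most of the usual route from predictability to bias is closed. Written consent comes before the physician is asked for INR data, so the stratum is unknown at consent, and others may be randomized in between. INR eligibility is a rule on the number and spacing of results, applied to data from the physician. The primary outcome rests on INR results supplied by family physicians, the evaluators are blinded, and the coordinator is said to have no clinical patient interactions. Varying the block size already keeps certain assignments near 11 %, against 33 to 50 % with a fixed size. All of this stands, and it limits the point to the period between receipt of the INR data and the randomize step.

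A reader might also infer stronger facts that the article does not give:
- **One coordinator handles every patient and sets the call order.** Recruitment speaks of the study coordinator, Randomization and allocation of a study coordinator. One person is a fair reading but is not stated, and control of the call order is not stated at all.
- **The coordinator knows the block sizes.** The article neither says so nor says that they are withheld; a condensed article may leave that to the full protocol.
- **The block sizes were public during recruitment.** Trial status shows recruitment only at submission, not at publication.
- **The primary comparison is exposed through the diet rating.** That rating is the patient's own report. It enters the subgroup analysis and the baseline cross-sectional regression, not the primary comparison.

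Finally, larger blocks lower the overall guess rate only from 72 % to 68 %. That is true, but the gain lies in the assignments someone could act on: certain ones fall from about 11 % to about 2 %, and highly predictable ones from 55 % to 23 or 24 %.

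**Conclusion.** The point holds as a limited, preventable risk. The block sizes and the joint role of interviewer and randomizer are both stated, and together they make the assurance about concealment stronger than the design supports. The headline figures (about 72 % guessable, 11 % certain, 55 % highly predictable) rest on equal mixing of the two sizes and on a coordinator who knows the sizes and tracks past assignments. If the sizes are withheld or several coordinators share the work without seeing each other's allocations, they are upper values. They measure what could be foreseen, not what was acted on. Nothing in the article shows selective enrolment or a biased primary result. A cheap improvement is advisable.

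**What to change.** For whatever allocations remain:

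1. Replace blocks of 2 or 4 with larger varied blocks, for example 4, 6 and 8, and withhold the sizes from the coordinator until recruitment ends.
2. Make randomization calls in the order in which eligible baseline INR data are received. The article already places the call after receipt; this adds the order.
3. Save and lock the baseline interview in REDCap before the randomize step opens. The article already collects these items first; the lock makes that verifiable.
4. Reword the text so that the module is said to conceal the list, and the block scheme and call order to limit prediction.

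The cost is a new allocation table and a line or two of procedure. The final imbalance could reach 4 per stratum rather than 2. At worst that is 3 × 4 = 12 overall, or 106 against 94 of 200, an effective group size of 2 × 106 × 94 / 200 = 99.6 instead of 100. Steps 2 and 3 help even if the table can no longer be changed. The article does not say how many allocations were still to come, so the benefit of step 1 depends on that number.
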